##### Intrinsic motivation inventory

Finally, brief self-report motivation questionnaires (that is, the Intrinsic Motivation Inventory) [103] will be provided to patients to complete prior to training, during training (that is, one time approximately half-way through training), and immediately post-training. This questionnaire will measure motivation, engagement, and self-regulation.

### Procedure

In the first session, following informed consent (consent form provided in Additional file 3), demographic information will be collected and the Vocabulary and Matrix Reasoning subtests of the WASI-II will be administered by trained graduate students. Next, the trained students will interview participants with the SCID-5. Finally, the PANSS will be administered. The entire first session should last approximately 3 hours and 35 minutes.

The second session will include pre-assessment of all neurocognitive, social cognitive, and functioning measures described above. This session will be approximately 2 hours and 45 minutes in duration. To reduce the impact of fatigue and carryover effects on the results, the administration order of all cognitive and functional measures will be counter-balanced using a Williams Design Latin Square [104]. Testing will be administered by trained graduate students and research assistants, who will be blind to the randomization until completion of the baseline assessment. Blinding will only be broken if knowledge of the patient’s treatment group is necessary for further patient management. Following the baseline assessment, participants will be randomized and provided with training instructions, including how to access the online training in addition to the training schedule. Training program names (for example, *Bubble Math*, *Moving Memory*) will not be concealed; however, participants will not be informed of the objectives or hypotheses of the current study, and will be unaware of the other training conditions. Participants will be contacted half way through training (after approximately 5 weeks) to complete the mid-point motivation questionnaire.

The 3 hour 30 minute post-training assessment will be composed of the same measures (that is, neurocognitive measures, social cognitive measures, and measures of functional status) described above and using parallel forms where indicated, in addition to a re-administration of the PANSS. All post-assessments will be conducted by trained graduate students and research assistants who are blind to the randomization of each participant. All assessment materials will be scripted to ensure consistency across examiners and across assessments.

### Adverse events

Participants will be asked to provide personal information about their own and their family history of mental and medical disorders. Revealing this personal information may lead to discomfort or may evoke unpleasant memories and/or anxiety. If a participant becomes upset during the diagnostic interview, the researcher will stop, provide support, and provide the participant the chance to decide whether they want to discontinue, reschedule, or continue. The interview will be conducted by trained research assistants or graduate students, who will appropriately deal with any anxiety or stress related to the interview. Community resources will be provided to individuals who are distressed and would like to talk to someone about the experiences that have been brought up in the interview.

In recognition of the high level of concentration needed to complete a single session of training and the commitment needed to sustain training over several weeks, we have decided to keep the training to absolute minimal levels for which the literature has indicated effects. Beyond keeping the cognitive demands from training to a minimum, we will be careful to protect participants emotionally by not exposing them to how their performance on any of the tasks relates to that of others. Due to the nature of adaptive training tasks, participants will be able to tell if their performance has improved session by session; however, no explicit feedback will be provided by the researchers. Participants are allowed to discontinue participation in the study at any point without any penalty to them.

### Data sets analyzed

All eligible participants who are randomized into the study and complete at least 50 % of the cognitive training will be included in the completer analysis, following similar cut-offs in prior cognitive training research [Lawlor-Savage L, Goghari VM: Dual n-back working memory training in healthy adults: a randomized comparison to processing speed training, submitted]. All eligible participants who are randomized into the study will be included in the intent-to-treat analysis. Data collection will stop when the goal sample size has been reached or when new participants are unable to be recruited for a significant period.

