## Methods/Design

### Study design

This study is a randomized controlled trial (RCT) and will be conducted at the Foothills Medical Centre and the University of Calgary in Calgary, Alberta, Canada. Participants who meet eligibility criteria will be randomly allocated to a working memory-training group, a processing speed-training group, or a no-training control group. The study will employ a parallel design with a 1:1:1 allocation ratio. Participants allocated to the working memory-training group or processing speed-training group will directly receive the specified cognitive training intervention, whereas those allocated to the no-training control group will be given the opportunity to receive one of the two cognitive training interventions after a waiting period of 10 weeks. Assessments are planned both before and after the intervention for the experimental groups, and both before and after the 10-week wait period for the control group.

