### Recruitment process and study population

Up to 81 schizophrenia patients will be recruited. This is based on a power calculation with an alpha-level of .05, power of .80, and an effect size of *d* = .70, with the effect size derived from a recent study examining a more specific cognitive remediation program (that is, auditory working memory training) in schizophrenia [58]. Importantly, this sample size accounts for dropout rates of up to 10 %, based on previous cognitive training studies [82]. Recruitment status is currently pending, with plans to start in January 2016. Patients will be recruited through outpatient clinics at Foothills Medical Centre and through community support programs in Calgary, Alberta, after receiving appropriate permissions to enter the clinics and discuss the study. Participants will also be recruited through an existing participant database at the University of Calgary. Inclusion criteria for all participants will be as follows: (1) a diagnosis of schizophrenia or schizoaffective disorder, assessed with the Structured Clinical Interview for DSM-5 (SCID-5) interview; (2) age 18 to 65 years; (3) no uncorrected visual impairment, including color blindness, determined by self-report; (4) no uncorrected hearing impairment, determined by self-report; and (5) able to provide informed consent, determined by the clinical experience of the researchers. Exclusion criteria will be as follows: (1) meeting Diagnostic and Statistical Manual - 5^th^ edition (DSM-5) diagnostic criteria for a current major depressive episode, manic episode, or hypomanic episode, assessed with the SCID-5 interview; (2) use of electroconvulsive therapy (ECT) or transcranial magnetic stimulation therapy (TMS) within the past month, determined by self-report; (3) recent (that is, within past 3 months) history of substance-use disorder (excluding nicotine, cannabis, or caffeine), assessed with the SCID-5 interview; (4) diagnosed with a medical condition known to affect cognition (for example, endocrine disease or uncontrolled diabetes), determined by self-report; and (5) score less than 70 on the Wechsler Abbreviated Scale of Intelligence (WASI-II). In addition, only individuals who have access to the internet on a home computer will be eligible to participate in the study.

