### Discontinuation of participants

Participants will be discontinued from the study if they withdraw their consent. Participants may be withdrawn from the study if they experience a significant increase in schizophrenia symptoms.

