### Statistical analysis

The following demographic variables at screening will be summarized: ethnicity, sex, age, and education. Between-group analyses of variance (ANOVAs) and chi square analyses will be used to examine any baseline differences between groups in demographics, individual characteristics (for example, sleep), cognition, and/or functioning. Any baseline differences will be corrected in all further analyses as appropriate.

Next, a three-group (working memory training, processing speed training, or no training) x time (pre-training or post-training) repeated measures ANOVA will be conducted to test for significant group differences in each domain of neurocognition (that is, memory, processing speed, executive functioning, and fluid intelligence) over time. Follow-up one-way repeated measures ANOVAs will be conducted as necessary to further examine the main effects of time. Follow-up independent *t*-tests will be conducted to examine differences in training- related gains between each training group and the no-training control group, based on the above-described *a priori* study objectives. Cohen’s *d* effect sizes will be reported. Notably, composite measures will be used where applicable (for example, a working memory composite, a processing speed composite).

Similarly, a group x time repeated measures ANOVA will be conducted to test for significant group differences in each social cognition task and each measure of daily functioning, with follow-up one-way repeated measures ANOVAs to follow-up on main effects of time and independent *t*-tests to examine group differences. Again, Cohen’s *d* effect sizes will be reported.

Finally, exploratory simple regression analyses will be conducted to examine potential moderating factors of training-related change. For any aspects of cognition and functioning that show significant training-related gains, regression analyses will be conducted using individual difference variables (for example, medication usage, sleep quality, duration of illness, intrinsic motivation) as the independent variable and change scores for each cognitive or functional domain as the dependent variable.

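### The intent-to-treat analysis promises all randomized participants, but the named pre/post tests use only those with both assessments, and the article provides for no imputation

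*Protocol article*

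**What the plan says.** Three statements in the protocol article bear on this point.

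- **Analysis sets** (Data sets analyzed): "All eligible participants who are randomized into the study will be included in the intent-to-treat analysis". A separate completer set takes those who "complete at least 50 % of the cognitive training will be included in the completer analysis".
- **Expected loss** (Recruitment process and study population): "this sample size accounts for dropout rates of up to 10 %, based on previous cognitive training studies". Under Discontinuation of participants, "Participants will be discontinued from the study if they withdraw their consent", and a marked rise in symptoms may also lead to withdrawal.
- **Tests** (Statistical analysis): a three-group "x time (pre-training or post-training) repeated measures ANOVA will be conducted to test for significant group differences in each domain of neurocognition", followed by independent "tests will be conducted to examine differences in training- related gains between each training group and the no-training control group". The regressions also use change scores. The section names no imputation and no likelihood-based model. It does say, in loose terms, that baseline differences between groups will be corrected in later analyses where suitable.

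On timing, Study design says: "Assessments are planned both before and after the intervention for the experimental groups", and likewise around the 10-week wait for controls. The mid-point contact collects only the motivation questionnaire.

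**The concern.** A participant without a post-test has no gain score, and no intermediate cognitive or functional measurement could stand in for it. The named tests therefore do not, by themselves, deliver the population that the intent-to-treat definition promises.

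Loss could plausibly differ between arms. Trained participants are asked for 25 hours of training. Controls carry no such burden and are offered the games only after their post-assessment, which gives them a reason to return. If loss differs by arm and depends on baseline level, a comparison of unadjusted gains is biased. If it depends on failure to benefit, a complete-case comparison overstates the effect in all randomized participants. The two errors run in opposite directions, so the result could not be called conservative. Either way, readers would take it as intent-to-treat.

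**Working it through.** **Inputs from the article:** 81 randomized, 27 per arm; dropout up to 10%; effect d = 0.70; two assessments.

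**Assumptions, not in the article:** pre-post correlation ρ of .6, .7 or .8; common SD of 1 at each assessment; for steps 3 to 5, 10% dropout in one trained arm (about 3 of 27) and none in control.

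**The plan's own figure.** The stated total of 81 was not reproduced with its dropout allowance. A two-sided pairwise comparison needs 33 per arm (99 in all), or 37 per arm (111) after dropout. A one-sided one needs 26 per arm (78), or 29 (87) after dropout. A three-group ANOVA with f = 0.35 needs 82 before dropout and about 90 to 91 after. That is a separate matter. Here 81 only sets how many participants are at stake.

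**Step 1: what the test uses.** With two time points, the group-by-time F test is the one-way ANOVA on post minus pre. A missing post score removes the participant. In a simulated data set of 81 with 8 post scores missing, the test used 73.

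**Step 2: how many.** 81 × 0.9 = 72.9 with both assessments, so 81 × 0.1 = 8.1, about 8, contribute nothing. Per arm, 27 × 0.9 = 24.3 remain.

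**Step 3: loss of low-baseline participants.** Let δ be the rise in the trained arm's mean baseline among those who stay. Their mean post score rises by ρδ and their mean pre score by δ, so the bias in the gain contrast is −(1 − ρ)δ.

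- If exactly the lowest 10% leave, δ = φ(1.2816)/0.9 = 0.1755/0.9 = 0.195.
- If loss only leans towards low scores, the simulated biases below imply δ of about 0.167 (0.067/0.4).

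| ρ | Leaning loss (simulated) | Lowest 10% lost: −(1 − ρ) × 0.195 |
|---|---|---|
| .6 | -0.067 | -0.078 |
| .7 | -0.050 | -0.058 |
| .8 | -0.034 | -0.039 |

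The range is about -0.03 to -0.08 SD. In the same scenarios the baseline-adjusted estimate had a bias of about zero (within 0.003).

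For scale, the standard error of the gain contrast is √[2(1 − ρ)] × √(1/27 + 1/24.3) = √[2(1 − ρ)] × 0.280. That is 0.250 at ρ = .6 and 0.177 at ρ = .8. The bias is therefore about 0.2 to 0.3 of a standard error.

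**Step 4: precision.** The residual variance is 2(1 − ρ) for gains and 1 − ρ² after baseline adjustment. The ratio is (1 + ρ)/2 = 0.80, 0.85 and 0.90, so adjustment lowers the variance by 20%, 15% and 10%.

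**Step 5: dropouts who got no benefit.** If 10% of the trained arm leave with zero benefit, the effect over all randomized is 0.9 × 0.70 = 0.63. Those who stay still show 0.70, an overstatement of 0.70/0.63 − 1 = 11%. The baseline-adjusted model also gives 0.70, so it does not correct this.

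**The case against.** The strongest reply is that the article defines a set, names tests and allows for dropout, and that imputing post scores before the ANOVA would satisfy all three. Missing-data handling is commonly left to a fuller plan, which is not shown. This stands in part. A reader might infer that the three statements cannot all hold, or that the intent-to-treat result is bound to be a complete-case one. The documents support neither. What remains is that the article fixes methods which, run as named, omit participants its own definition includes.

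A reader might also infer that the intent-to-treat set shrinks to nearly the completer set. That is unsupported. Completers are defined by training dose, not attendance, so someone with under 50% of the training who attends post-testing stays in the intent-to-treat analysis. Nothing in the article says that those who stop training also miss the post-test.

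The size is modest. Dropout of 20% would give larger figures but exceeds the stated allowance, so it is not used. Nor does a mixed model recover information from participants with only a baseline score. With two time points and complete baselines, it gives essentially the same contrast as ANCOVA on those with a post score. The bias in step 3 is due to unadjusted gains, not to complete cases as such.

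Finally, the baseline-correction sentence might seem to cover step 3. It does not do so reliably. It depends on a difference being noticed at baseline, whereas this imbalance arises afterwards, through loss. Even among those who remain, a shift of 0.167 to 0.195 SD is only 0.6 to 0.7 of its standard error (0.280), so a significance test would seldom flag it.

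A separate conflict lies under Concurrent therapy, where participants who change type of treatment are left out of the analysis with no exception for intent-to-treat. Imputation would not resolve it. Those sections should be reconciled too, but this point does not rest on them.

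**Conclusion.** The concern holds in limited form. As named, the tests do not deliver the all-randomized population. Without imputation, about 8 of 81 participants, at the plan's own 10% dropout, would contribute nothing to the analysis labelled intent-to-treat.

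The consequence depends on why participants leave. With 10% loss in one trained arm, mainly at low baseline, and ρ of .6 to .8, the gain contrast is biased by about -0.03 to -0.08 SD, and baseline adjustment removes this. With 10% loss of participants who gained nothing, the estimate is 0.70 against 0.63, and baseline adjustment does not help. The article gives no figure for ρ, for the split of dropout by arm or for the reasons, so these sizes are illustrations. The point should be settled before recruitment starts, but it does not threaten the trial as a whole.

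**What to change.** 1. **Main contrast** (Statistical analysis). Adjust each training-versus-control comparison for the baseline score in every participant, whether or not a baseline difference is detected. Use a likelihood model with pre and post scores as outcomes and a common baseline mean across arms, or ANCOVA on the post score. This is valid if dropout depends on baseline and arm, and it has 10-20% lower variance than gains at the correlations considered.
2. **Sensitivity analysis.** Multiply impute missing trained-arm post scores from the control arm. This addresses dropouts who got no benefit, which the main model cannot.
3. **Label** (Data sets analyzed). If the ANOVA is kept without imputation, call the set randomized participants with both assessments and drop the intent-to-treat name.

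The cost is a change of wording and a little more programming, with no new visits, data or participants. Baseline testing already precedes randomization, and recruitment had not begun when the article was written. The one drawback is that the sensitivity estimate will be somewhat smaller than the main one.

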### Statistical analysis

The following demographic variables at screening will be summarized: ethnicity, sex, age, and education. Between-group analyses of variance (ANOVAs) and chi square analyses will be used to examine any baseline differences between groups in demographics, individual characteristics (for example, sleep), cognition, and/or functioning. Any baseline differences will be corrected in all further analyses as appropriate.

Next, a three-group (working memory training, processing speed training, or no training) x time (pre-training or post-training) repeated measures ANOVA will be conducted to test for significant group differences in each domain of neurocognition (that is, memory, processing speed, executive functioning, and fluid intelligence) over time. Follow-up one-way repeated measures ANOVAs will be conducted as necessary to further examine the main effects of time. Follow-up independent *t*-tests will be conducted to examine differences in training- related gains between each training group and the no-training control group, based on the above-described *a priori* study objectives. Cohen’s *d* effect sizes will be reported. Notably, composite measures will be used where applicable (for example, a working memory composite, a processing speed composite).

Similarly, a group x time repeated measures ANOVA will be conducted to test for significant group differences in each social cognition task and each measure of daily functioning, with follow-up one-way repeated measures ANOVAs to follow-up on main effects of time and independent *t*-tests to examine group differences. Again, Cohen’s *d* effect sizes will be reported.

Finally, exploratory simple regression analyses will be conducted to examine potential moderating factors of training-related change. For any aspects of cognition and functioning that show significant training-related gains, regression analyses will be conducted using individual difference variables (for example, medication usage, sleep quality, duration of illness, intrinsic motivation) as the independent variable and change scores for each cognitive or functional domain as the dependent variable.

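### The plan analyses change scores and adjusts only for baseline differences found by testing; a pre-specified ANCOVA on the pre score would be more precise at almost no cost

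*Protocol article*

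**What the plan says.** The Statistical analysis section of the protocol article fixes three things.

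- **Baseline screening.** ANOVAs and chi-square tests "will be used to examine any baseline differences between groups in demographics, individual characteristics", and also in cognition and functioning. The rule that follows is "Any baseline differences will be corrected in all further analyses as appropriate". It names no covariate, threshold or method of correction.
- **Main test.** A three-group by two-time repeated measures ANOVA for each domain, on composites where applicable.
- **Contrasts serving the a priori objectives.** Independent *t*-"tests will be conducted to examine differences in training- related gains between each training group and the no-training control group".

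The section on pre-training and post-training measures has the outcome battery given before randomization and again after training, so a pre score exists for every primary composite. The Recruitment section gives the planning values: "Up to 81 schizophrenia patients will be recruited", from a "power calculation with an alpha-level of .05, power of .80" and "an effect size of *d* = .70", and it states that "this sample size accounts for dropout rates of up to 10" %.

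**The concern.** With exactly two time points, the group by time interaction is the same test as a one-way ANOVA on post minus pre. The follow-up t-tests on gains are the pairwise version of it. Both subtract the whole pre score, so they impose a slope of 1 of post on pre. When the true slope is below 1, as it is for any r below 1 with equal SDs, subtraction over-corrects and leaves avoidable noise in the contrast. ANCOVA estimates the slope instead.

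The plan's only route to a better adjustment is a correction triggered by a baseline difference test. Allocation is by complete randomization, so any such difference arises by chance. How large it is says nothing about whether the variable predicts outcome, and prognostic value is what makes a covariate worth adjusting for. The correction also sits awkwardly with the follow-up analysis, because an independent t-test takes no covariate.

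At stake is precision in the training-versus-control contrasts of a trial with 27 per arm, together with a covariate set that is left open until the data are seen.

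**Working it through.** **Inputs from the article:** 81 randomized 1:1:1, so 27 per arm; dropout up to 10%, and 27 × 0.9 = 24.3, taken as 24; alpha .05; power .80; d = .70.

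**Assumptions, because the article does not give them:** two-sided test; equal pre and post SDs and a common slope; r of .5 to .8, with .3 and .9 as outer values; d in SD units either of the post score or of the change.

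**Step 1. The plan's own figure.** A two-sided t-test at d = .70 and 80% power needs 34 per arm (33 by normal approximation). That is 102 in total, or 102/0.9 → 114 with dropout. Power is .71 at 27 per arm and .66 at 24. One-sided, the need is 26 per arm, 78 in total, or 87 with dropout. A one-way three-group ANOVA with f = .35 needs 82, or 91 with dropout. None of these gives 81 with the dropout allowance included. That is a separate matter; here it only fixes 24 per arm as the working size.

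**Step 2. Residual variances, in post-score SD² units.**

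- Change score: 2(1 − r)
- ANCOVA: 1 − r² = (1 − r)(1 + r)
- Ratio ANCOVA/change: (1 + r)/2

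| r | .3 | .5 | .6 | .7 | .8 | .9 |
|---|---|---|---|---|---|---|
| Ratio | .65 | .75 | .80 | .85 | .90 | .95 |

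Simulated three-arm trials with 24 per arm gave ratios of .76–.77 (r = .5), .87 (r = .7) and .92–.93 (r = .8). These are slightly above the formula because the slope has to be estimated. ANCOVA type I error was 4.9–5.1%.

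**Step 3. Power at 24 per arm** (noncentral t; 46 df for gains, 45 for ANCOVA).

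If d is in post-score SDs, the effective d is .70/√(2(1 − r)) for gains and .70/√(1 − r²) for ANCOVA. At r = .5 these are .700 and .808; at r = .7 they are .904 and .980.

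If d is in change-score SDs, the effective d is .70 for gains at every r and .70/√((1 + r)/2) for ANCOVA.

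| r | Post-SD: gains | Post-SD: ANCOVA | Change-SD: gains | Change-SD: ANCOVA |
|---|---|---|---|---|
| .3 | .52 | .70 | .66 | .84 |
| .5 | .66 | .78 | .66 | .78 |
| .6 | .76 | .84 | .66 | .76 |
| .7 | .87 | .91 | .66 | .73 |
| .8 | .96 | .98 | .66 | .71 |

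**Step 4. What the conditional rule achieves.** The rule was simulated as ANCOVA on the pre score only when the three-arm baseline ANOVA has p < .05, and the gain t-test otherwise. It fired in about 5% of trials per outcome and cut variance by 1–5%. At r = .5 power was 66.5%, against 65.8% with no adjustment and 77.4% with ANCOVA always. Type I error was 4.7–4.9%.

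**Step 5. How often something is flagged.** The article states neither the number of baseline tests nor a threshold. If 20 to 25 tests were made at 5% and were independent, the chance of at least one flag would be 1 − .95²⁰ = .64 to 1 − .95²⁵ = .72. Correlated measures lower this: with 25 variables, simulation gave about .61 at an inter-correlation of .3 and .48 at .5. So .72 is an upper figure.

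**The case against.** The strongest reply is that the planned analysis is sound. Under randomization the gain contrast is unbiased and its test is valid. The choice of change score or ANCOVA is then one of efficiency, and the covariate list is the kind of detail that a statistical analysis plan, not shown here, may settle. The validity part stands in full. The second part stands only in part, because the article itself fixes the test, the contrasts and the rule for adjustment, and there is a better choice at almost no cost.

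A reader might draw four stronger conclusions that the documents do not support.

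- **That the p-values are invalid.** They are not. Type I error under the rule stayed at 4.7–4.9% with the pre score alone. It was 4.4–4.9% when 25 baseline variables were screened and every flagged one was added to a gain-score model.
- **That the baseline scores are discarded, or that the outcome's own pre score may be left out.** The pre score is one of the two time levels and is subtracted in every gain. What is missing is an estimated slope.
- **That ANCOVA restores the claimed 80% power.** This depends on two figures that are not given. With d in change-score SDs, ANCOVA stays at .78 to .71 for r = .5 to .8. With d in post-score SDs, the planned gain test itself passes 80% once r exceeds about .64.
- **That the gain is always large.** At r = .8 it is 10% of the variance, and at r = .9 it is 5%.

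**Conclusion.** The point holds as one of efficiency and pre-specification, not of validity. For every r below 1, with equal pre and post SDs, the planned change-score analysis is less precise than ANCOVA on the same data. The variance reduction is 25% to 10% for r = .5 to .8. The direction is certain apart from the single degree of freedom, which is negligible at 24 per arm unless r is near .95 or above. The size in power terms is conditional: between 2 and 12 percentage points for r = .5 to .8 if d = .70 is in post-score SDs, and between 5 and 12 points if it is in change-score SDs. The test-triggered correction recovers almost none of this, and it chooses covariates by chance imbalance instead of prognostic value. The change is recommended, but the trial's conclusions would not be invalid without it.

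**What to change.** - Make the primary model for each composite (working memory, processing speed, fluid intelligence) an ANCOVA of the post score on arm, adjusted for the pre score of the same composite.
- Read the two training-versus-control contrasts, with 95% confidence intervals, from that model in place of the separate t-tests on gains.
- Form order for the Raven and Cattell tests may be added as a factor for fluid intelligence. This is optional, since the forms are already counterbalanced.
- Report baseline data descriptively. Delete the baseline significance tests and the correction that depends on them, and name any further covariate in advance on prognostic grounds.
- When the sample size is restated, give the assumed pre-post correlation and the SD to which d = .70 refers.

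The cost is one residual degree of freedom and revised wording. No new data are needed.
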